Safety data were obtained from a total of 269 CML patients in 5 CML studies with safety and efficacy as primary or secondary endpoints. The data cutoff date for SJ-0002, CC201, and CC202 was 12 months after enrollment of the last patient; the data cutoff dates for CC203 and CU101 were May 25, 2021, and January 31, 2021, respectively. The mean treatment period of study drug was 13.1 (range: 0.2; 38.9) months. Approximately 99% of subjects experienced at least one treatment-emergent adverse event (TEAE), and most TEAEs were mild or moderate and could be resolved with or without interruption, dose reduction, or discontinuation of the study drug. The most common TEAEs ( $\geq 20\%$ ) included hematological abnormalities (reduced platelet count, white blood cell count decreased/neutrophil count decreased, and anemia), skin pigmentation, liver function test abnormal (ALT increased, AST increased, GGT increased, or blood bilirubin increased), metabolic disorder (hypertriglyceridemia, hypocalcemia), and others (pyrexia, proteinuria and blood creatine phosphokinase increased). 10% of patients withdrew from the study due to AEs. 26% of patients experienced SAEs, but no deaths due to AEs were reported. Based on the safety profile of HQP1351 in CML, reduced platelet count and anemia were the most frequently reported SAEs related to the study drug, and were identified as important risks of HQP1351 in the treatment of CML patients. Based on available data, HQP1351 is well tolerated in CML patients and has a positive benefit/risk ratio for CML patients who are resistant or intolerant to multiple TKIs. Data were obtained from 36 GIST subjects in the SJ-0003 study, including 3, 11, 11, and 11 subjects enrolled in 4 designated dose cohorts (20 mg QOD, 30 mg QOD, 40 mg QOD, and 50 mg QOD), and the safety analysis was based on a combination of the 4 dose groups. As of January 31, 2021, the mean duration of treatment for GIST patients was 2.5 (range 0.1-13.1 months) months. All subjects (100%) experienced at least one TEAE, and most TEAEs were mild or moderate and could be resolved or recovered with or without interruption, dose reduction, or discontinuation of the study drug. Among them, 5 (14%) subjects discontinued treatment due to AEs. The most common hematological AEs ( $\geq 20\%$  TEAEs) in GIST subjects included white blood cell count increased (63.9%), neutrophil count increased (52.8%), and anemia (41.7%). The most common non-hematological AEs ( $\geq 20\%$  TEAEs) included constipation (44.4%), asthma (38.9%), aspartate

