
[figure not shown]

aminotransferase increased (33.3%), hyperuricemia (33.3%), hypoproteinemia (27.8%), alanine aminotransferase increased (25.0%), serum creatinine increased (25.0%), abdominal pain (22.2%), and C-reactive protein increased (22.2%). Ten (28%) subjects experienced at least one serious adverse event (SAE), and GI tract obstruction, as the most commonly reported SAE in GIST patients, was due to PD of GIST and probably unrelated to HQP1351. Four (11%) subjects experienced fatal AEs, 1 due to renal failure, 1 due to intestinal perforation and septic shock arising from intestinal obstruction, 1 due to death unexplained (presumed by the investigator to be in the terminal stage of the disease), and 1 due to PD, all of which were assessed by the investigator as unlikely related to the drug. Available clinical data suggest that HQP1351 when dosed at 30 mg, 40 mg, and 50 mg is well tolerated in patients with CML and GIST.

Based on the safety data from 9 clinical studies that have been conducted with HQP1351 and the safety and efficacy data of 36 patients already enrolled in this study, 40 mg QOD is selected as the dosage for adult subjects after discussion between the investigator and the sponsor, and no randomization at 30 mg, 40 mg or 50 mg QOD will be performed.

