| Grade 1                                                                                                                                                                                                                                                                                                                                                                                                                                                                                                                                                                                                                               | 
 
1. Monitor liver function once a week.
 
2. No dose adjustment is required.
 
                                                                                                                                                                                                                                                                                                                                                                                                                                                                                                           |
| Grade 2: Total bilirubin $> 1.5 \times \text{ULN}$ and $\leq 3 \times \text{ULN}$                                                                                                                                                                                                                                                                                                                                                                                                                                                                                                                                                     | 
 
1. Increase the frequency of liver function monitoring (once every 2-3 days) until it recovers to baseline level.
 
2. Dose adjustment: 
 
a) If toxicity resolves to Grade <math>\leq 1</math> within 14 days (inclusive), resume HQP1351 administration at the original dose level.
 
b) If toxicity resolves to Grade <math>\leq 1</math> beyond 14 days, or toxicity recurs, resume HQP1351 administration at a reduced dose level.
 
c) If toxicity recurs after two dose reductions, stop HQP1351 administration.
 
 
 
 |

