| Confounding variables and/or other causes of total bilirubin increased should be excluded before dose interruption/reduction. They include, but are not limited to, evidence of obstruction (e.g., typical ALP and GGT increased due to gallbladder or bile duct disease), hyperbilirubinemia (i.e., direct bilirubin $\leq 1 \times \text{ULN}$ ) due to indirect bilirubin increased as a result of hemolysis or Gilbert syndrome, drug treatment, viral hepatitis, alcoholic or autoimmune hepatitis, and hepatotoxic drugs. For patients with Gilbert syndrome, these dose adjustments apply only to changes in direct bilirubin. |                                                                                                                                                                                                                                                                                                                                                                                                                                                                                                                                                                                                                                                |
| AST/ALT increased (without <math>> 2 \times \text{ULN}</math> total bilirubin increased)                                                                                                                                                                                                                                                                                                                                                                                                                                                                                                                                    |                                                                                                                                                                                                                                                                                                                                                                                                                                                                                                                                                                                                                                                |

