**The following assessments must be completed within 28 days prior to the first dose of the study drug:**

- The signing of the written informed consent form.
- Demographics: including age, gender, ethnicity and race.
- Diagnosis, tumor staging and objective disease assessment: including diagnosis, staging, histology/cytology, and lesion sites included in the study, including immunohistochemical testing of SDHB;
- Previous anti-tumor treatments (surgery, radiotherapy, drugs, etc.) (supporting documents of trial-related disease and medical history): all previous anti-tumor treatments, including all surgeries, chemotherapies, biotherapies, immunotherapies and radiotherapies, used for the treatment of tumors or as palliative treatment before the start of the study drug;
- Accompanying and past related medical history (including non-tumor history, history of drug allergy and history of drug dependence, etc.)
- Physical examination: The physical examination will include examination of the general condition, skin and mucous membranes, neck (including thyroid), skull, eyes, ears, nose, mouth and throat, thorax and breasts, lungs, heart, abdomen, back (including spine), lymph nodes, limbs, and basic nervous system assessment;
- Height and weight;
- Vital signs: blood pressure, pulse, respiratory rate and body temperature.

[figure not shown]

- Complete blood count with differential: hemoglobin, hematocrit, red blood cell count, white blood cell count and differential count, and platelet count. White blood cell differential count include neutrophil, lymphocyte, monocyte, eosinophil, and basophil counts (reported as absolute counts).
- Serum chemistry: C-reactive protein (CRP), sodium, potassium, magnesium, calcium, phosphorus, chloride, bicarbonate or carbon dioxide, albumin, urea or blood urea nitrogen, uric acid, creatinine, total bilirubin, AST, ALT, glucose, alkaline phosphatase, and triglycerides.
- HBV, HCV, HIV, treponema pallidum screening.
- Coagulation test: prothrombin time (PT) and activity, partial thromboplastin time (PTT)/activated partial thromboplastin time (APTT), fibrin degradation product, fibrinogen quantification, and D-dimer.
- Lipase and amylase.
- Urinalysis: Urine glucose, protein, bilirubin, urobilinogen, specific gravity, occult blood, pH value, ketone bodies, nitrite, white blood cells, turbidity, and color. A microscopic analysis will be performed if there is any abnormality in urinalysis.
- Tumor imaging assessment

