- Previous anti-tumor treatments (surgery, radiotherapy, drugs, etc.) (supporting documents of trial-related disease and medical history): all previous anti-tumor treatments, including all surgeries, chemotherapies, biotherapies, immunotherapies and radiotherapies, used for the treatment of tumors or as palliative treatment before the start of the study drug.
- At the screening visit only, height will be recorded.
- Vital signs include blood pressure, pulse, respiratory rate and body temperature. Measurements of vital signs prior to administration of HQP1351 on C1D1 are baseline values.
- Physical examination: A thorough physical examination including the general condition, skin and mucous membranes, neck (including thyroid), skull, eyes, ears, nose, mouth and throat, thorax and breasts, lungs, heart, abdomen, back (including spine), lymph nodes, and limbs and basic nervous system assessment will be performed at the screening visit, end of study/withdrawal visit (within 14 days after the last dose), and at the visit approximately 30 days after the last dose. At other visits, signs related to the disease may be directly examined.
- Complete blood count with differential: hemoglobin, hematocrit, red blood cell count, white blood cell count and differential count, and platelet count. White blood cell differential count include neutrophil, lymphocyte, monocyte, eosinophil, and basophil counts (reported as absolute counts).
- Serum chemistry: C-reactive protein (CRP), sodium, potassium, magnesium, calcium, phosphorus, chloride, bicarbonate or carbon dioxide, albumin, urea or blood urea nitrogen, creatinine, uric acid, total bilirubin, AST, ALT, glucose, alkaline phosphatase, and triglycerides.
- HIV/HBV/HCV screening: HBsAg\anti-HCV antibody\anti-HIV1/2 antibody.
- Coagulation test: prothrombin time (PT) and activity, partial thromboplastin time (PTT)/activated partial thromboplastin time (APTT), fibrin degradation product, fibrinogen quantification, and D-dimer.

[figure not shown]

12. Urinalysis: Urine glucose, protein, bilirubin, urobilinogen, specific gravity, occult blood, pH value, ketone bodies, nitrite, white blood cells, turbidity, and color. A microscopic analysis will be performed if there is any abnormality in urinalysis.
13. Echocardiography: The main parameters of echocardiography are left ventricular ejection fraction and heart structure.

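### The scheduled chemistry panel omits CPK, a common laboratory TEAE of this drug in CML, and provides no pre-dose direct bilirubin for Table 3's Gilbert rule

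*Protocol*

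**What the plan says.** The serum chemistry panel is spelled out visit by visit. At screening (Section 7.2.2) the list ends "uric acid, creatinine, total bilirubin, AST, ALT, glucose, alkaline phosphatase, and triglycerides". Footnote 9 of the Schedule of Assessments (Table 8), which defines serum chemistry for every visit that uses the term, ends "creatinine, uric acid, total bilirubin, AST, ALT, glucose, alkaline phosphatase, and triglycerides". The end-of-treatment and Day 30 visits say only serum chemistry, so they inherit that definition.

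The drug's safety history is in Section 1.5.2. In 269 CML patients from five studies, the TEAEs occurring in at least 20% include "others (pyrexia, proteinuria and blood creatine phosphokinase increased" and, as one grouped item, "liver function test abnormal (ALT increased, AST increased, GGT increased, or blood bilirubin increased". For the 36 GIST subjects in this study, the list at the same threshold ends with "abdominal pain (22.2%), and C-reactive protein increased (22.2" percent. It contains neither CPK nor GGT.

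Table 3 governs dosing for isolated bilirubin rises. It asks that other causes be excluded first, giving as one example "evidence of obstruction (e.g., typical ALP and GGT increased due to gallbladder or bile duct disease", and it describes indirect hyperbilirubinemia by a direct bilirubin no higher than the ULN. It then adds: "For patients with Gilbert syndrome, these dose adjustments apply only to changes in direct bilirubin". For Grade 2 and Grade 3 it also says: "Increase the frequency of liver function monitoring (once every 2-3 days) until it recovers to baseline level".

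Section 10.2.1 makes clinical laboratory tests part of the primary endpoint.

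**The concern.** A laboratory toxicity can be counted only in subjects who were tested. The protocol's own summary identifies CPK elevation as a common event with this drug, the trial's primary question is safety, and yet no visit schedules a CPK. Two later steps then rest on a test that may not exist. Section 9.2.3 turns an abnormal result into an adverse event when the investigator judges it clinically significant, for example because it is new or worse than at baseline. Section 4.3.2 interrupts drug for related Grade 3 or 4 toxicity. If CPK is measured at one site and not at another, the reported rate reflects ordering habits, its true denominator is unknown, and no later analysis can recover the missing values.

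The second, smaller issue is internal to the document: Table 3 ties dosing in Gilbert syndrome to a change in an analyte for which no pre-dose measurement is planned.

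**Working it through.** **1. Is the omission real?** The analyte lists, set against where each analyte is used:

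| Analyte | In any scheduled chemistry list? | Where the protocol relies on or reports it |
|---|---|---|
| Total bilirubin, AST, ALT, ALP | Yes, at every listed chemistry visit | Table 3 |
| Direct bilirubin | No | Table 3: Gilbert rule and marker of indirect hyperbilirubinemia |
| CPK | No | Section 1.5.2: TEAE at or above 20% in CML |
| GGT | No | Section 1.5.2, inside a grouped term; Table 3, as an example beside ALP |

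The lists checked were screening, C1D1, C1D8, C1D15, C1D22, C2D1, C2D15, Day 1 of Cycle 3 onward, C3D15/C4D15, and Table 8 footnote 9. Scheduled pre-dose measurements: direct bilirubin 0, CPK 0, GGT 0.

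**2. What do the 36 GIST subjects show about CPK?** The threshold is 0.20 × 36 = 7.2 subjects. Eight of 36 is 22.2%, which equals the lowest rates on the list. Seven of 36 is 19.4%, which would not be listed. If the list is complete, at most 7 CPK cases were recorded, and every count from 0 to 7 fits. The number of subjects tested is not given, so a low true rate and a lack of testing cannot be told apart. Most of the listed laboratory events (white cells, neutrophils, anemia, AST, ALT, uric acid, creatinine, CRP) correspond to scheduled tests. That pattern fits reporting that follows the panel, but it proves nothing about CPK.

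**3. Does the Gilbert rule fail without a baseline?** In the isolated-bilirubin rows of Table 3, the grades are multiples of ULN: above 1.5 up to 3 for Grade 2, above 3 up to 10 for Grade 3, above 10 for Grade 4. Decisions to resume, reduce or stop turn on return to Grade 1 or below, on whether this takes more than 14 days, and on recurrence. Recovery to baseline in those rows only sets how long the intensified monitoring lasts. Baseline does drive dosing in the AST/ALT rows, but AST and ALT are scheduled. A direct bilirubin drawn at the event and read against ULN is therefore enough to act on. What is lacking is the value from which a change would be measured.

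**4. How many subjects does the Gilbert gap touch?** The documents give no count of subjects with Gilbert syndrome. Inclusion criterion 6 caps total bilirubin at 1.5 × ULN with no Gilbert exemption, so few are likely to enter.

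**The case against.** The strongest reply is that panel content is a matter of choice. No dose rule, eligibility criterion or planned analysis names CPK, and including laboratory tests in the endpoint does not promise this particular one. The CPK evidence comes from CML patients, while this trial's own 36 GIST subjects do not show it at 20% or more. Section 7 already requires unscheduled examinations when clinically indicated and recording of all laboratory results, so what could be missed is mainly symptom-free rises. Most of this stands, and it is why the priority is low. It does not remove the point: the protocol itself reports CPK elevation as common with this drug, and the GIST list cannot reassure when testing was never scheduled.

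For GGT the reply largely succeeds. Its own rate is not given, Table 3 mentions it only as an example beside the scheduled ALP, and hepatic safety is followed through ALT, AST, ALP and total bilirubin.

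A further objection is that scheduling CPK has a clinical price. Symptom-free rises would meet the Grade 3–4 interruption rule in Section 4.3.2. Under the other-toxicities rows of Table 4, a Grade 4 value stops the drug. This is correct, and the fix must deal with it.

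A reader might also infer that the Gilbert rule cannot be applied, or that bilirubin dose decisions need a baseline direct value. Neither follows. The decisions rest on ULN-based grades and recurrence, and Table 3 and Section 7 already lead to a test at the event.

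**Conclusion.** The point holds in a limited form. CPK is absent from the scheduled panel although it is a known common laboratory event of this drug, so its capture in a primary safety endpoint depends on site practice. This is a risk of under-ascertainment. It is tempting to conclude that CPK cases were missed in the 36 GIST subjects, but the documents give neither a GIST rate nor a number tested, and between 0 and 7 recorded cases are all compatible with the published list. The number missed cannot be estimated.

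The lack of a pre-dose direct bilirubin is a gap in the starting value only, affecting few subjects and blocking no dose decision.

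The conclusion assumes that the chemistry lists are exhaustive and that the CML experience is relevant to GIST patients. Correcting the panel now would not improve the comparison of 30, 40 and 50 mg, because Section 1.5.2 ends randomization. The gain is a CPK rate at 40 mg with a known denominator. Low priority: a cheap improvement.

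**What to change.** Amend Table 8 footnote 9 and the chemistry lists in Sections 7.2.2 to 7.5.2 as follows:

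- **CPK:** at baseline and every scheduled chemistry visit for subjects still to be enrolled, and at the remaining chemistry visits for those on treatment. Report the number tested beside the Safety Set denominator.
- **Direct bilirubin:** at baseline and whenever total bilirubin is raised.
- **GGT:** optional.
- **Handling rule:** state that an isolated CPK rise without symptoms is confirmed by a repeat test and reviewed with the sponsor before permanent discontinuation, so that the Table 4 Grade 4 row does not end treatment on a single unconfirmed value. The amendment should also say how the Grade 3–4 interruption in Section 4.3.2 applies to such rises.

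The cost is a small assay charge on blood already drawn, an amendment with its approvals, and an eCRF update. Subjects already on treatment will have no baseline CPK under the new schedule. The CPK data will mix an unscheduled and a scheduled period, and the report must say so and show them separately. Some symptom-free rises will come to light that would otherwise have gone unseen, with extra repeat tests and possible dose interruptions.
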